#### Methods of additional analyses

Both the primary and secondary outcomes will be analyzed by logistic regression, controlling for three, prespecified, potential confounding variables, i.e., age, sex, and subtype of IBS. The difference between study groups will be considered significant when the *p* value is < 0.05, when the 95% CI for RR (or odds ratio [OR]) does not include 1.0, or when 95% CI for MD does not include 0. All statistical tests will be two-tailed and performed at the 5% level of significance.

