#### Eligibility criteria

##### Inclusion criteria

At enrollment, the volunteer children must fulfill all of the following eligibility criteria to be considered for inclusion: (1) age at least 8 years and ≤ 18 years (regardless of race, ethnicity, gender); (2) FAP-NOS or IBS diagnosed according to the Rome IV Criteria [2]; (3) baseline average pain intensity at least 30 mm on a 100-mm Visual Analogue Scale (VAS) [9]; (4) feeding via the oral route; (5) ability to read and comprehend any employed questionnaires/scales; (6) signed informed consent; and (7) stated availability throughout the study period.

Participants with IBS and a stool consistency score > 5 on the Bristol Stool Scale will be classified as having IBS with predominant diarrhea (IBS-D); if the stool consistency score is < 3, the subjects will be classified as having IBS with predominant constipation (IBS-C) [16].

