**Change in stool consistency.** Responders will be subjects with improvement in their average stool consistency during the last week of the trial compared with baseline [≥1 higher Bristol Stool Scale score in case of IBS-C, or at least one lower score in case of IBS-D] [16]. The change at weeks 1, 2, and 3 from baseline also will be measured.**Change in abdominal pain frequency** at weeks 1, 2, 3, and 4 from baseline [16].**Change in GSRS** [21] **total score** at weeks 1, 2, 3, and 4 from baseline.**Change in KIDSCREEN-10 index** [22] **total score** at weeks 1, 2, 3, and 4 from baseline.**Change in WHO-5** [18] **total score** at weeks 1, 2, 3, and 4 from baseline.**Change in percentage of school attendance** associated with IBS symptoms (at weeks 1, 2, 3, and 4 from baseline).**Change in percentage of parents’ work absenteeism** associated with IBS symptoms in child (at weeks 1, 2, 3, and 4 from baseline).**Change in BMI-for-age z-score**. The BW (kg) and standing height (cm) will be measured following standard methods by an independent nurse at baseline, after 2 weeks, and after 4 weeks. Body Mass Index (BMI) will be calculated using the standard eq. BMI-for-age z-score will be computed using the WHO AnthroPlus software v1.0.4., then assessed and monitored over time using the WHO growth charts by a dietitian.**Percentage of compliant participants** (see Compliance section).**Percentage of tolerability of the low-FODMAP diet.** This outcome will be reported as a mean for each study group, and as a comparison between groups (MD [mean difference] with 95% CI).**Adverse events.** The number of all adverse events and the number of participants reporting adverse events associated with the intervention (with characteristics) will be reported for each study group (see Criteria for discontinuing the intervention and Harms sections).

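### The adjusted analysis names logistic regression for continuous outcomes and a covariate, IBS subtype, that has no value for FAP-NOS children or for IBS children scoring 3 to 5

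*Protocol article*

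**What the plan says.** All references are to the protocol article.

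- **Model.** Methods of additional analyses: "Both the primary and secondary outcomes will be analyzed by logistic regression". No outcome is excepted and no other regression model is named anywhere in the article.
- **Covariates.** The same sentence continues "controlling for three, prespecified, potential confounding variables, i.e., age, sex, and subtype of IBS".
- **Significance rules.** The same paragraph counts a result as significant by the p value, by the CI for the RR or OR, "or when 95% CI for MD does not include 0".
- **Population.** Inclusion criteria: "FAP-NOS or IBS diagnosed according to the Rome IV Criteria". The study hypothesis names both diagnoses.
- **Subtype definition.** Inclusion criteria: "Participants with IBS and a stool consistency score > 5 on the Bristol Stool Scale will be classified" as IBS-D, and "if the stool consistency score is < 3, the subjects will be classified as having IBS with predominant constipation (IBS-C"). No other level is given.
- **Outcomes.** The primary outcome is a responder definition. GSRS, KIDSCREEN-10 and WHO-5 are each specified as a change in "total score at weeks 1, 2, 3, and 4 from baseline". Other secondary outcomes are also changes or means.
- **Main analysis.** Data analysis plans t-tests or Mann-Whitney tests for continuous variables and chi-square or Fisher tests for percentages. It places all analyses on an intention-to-treat basis, covering every randomised child with outcomes available.

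**The concern.** Two parts of one sentence do not fit the rest of the plan.

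First, logistic regression models a binary outcome, and most of the secondary outcomes are not binary. Taken literally, the analyst must either dichotomise these scores at cut-offs that are not in the plan or replace the named model. Either choice would be made after data collection, and prespecification is meant to remove that freedom.

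Second, a covariate in a model for the whole trial needs a value for every child. IBS subtype has none for FAP-NOS children, who are half of the stated target population in kind if not in number, and none for IBS children with mid-range stool scores. If those children are treated as missing, the only covariate-adjusted analysis in the article would describe a narrower population than the hypothesis and the unadjusted tests do.

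**Working it through.** **1. Outcome types against the model.** The Outcomes section gives one primary and eleven secondary outcomes.

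| Outcome | Form in the plan | Logistic regression as named |
|---|---|---|
| Pain intensity (primary) | Responder: at least 30% and at least 25 mm | Suitable |
| Stool consistency | Responder, defined for IBS-C and IBS-D | Suitable |
| Compliance | Compliant or not (80% threshold) | Suitable |
| Adverse events | Number of events; number of children affected | Suitable for children affected only |
| Pain frequency | Change | Not suitable |
| GSRS, KIDSCREEN-10, WHO-5 | Change in score | Not suitable (3 outcomes) |
| School attendance, parents' absenteeism | Change in percentage | Not suitable (2 outcomes) |
| BMI-for-age z-score | Change | Not suitable |
| Tolerability | Mean per group, compared as MD | Not suitable |

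The unsuitable outcomes number 1 + 3 + 2 + 1 + 1 = 8. None of them is given a cut-off.

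As a direct check, change scores were simulated for 74 children (means of -20 and -30, SD 25; arbitrary values). Standard software refused the logistic model because the outcome must lie between 0 and 1.

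**2. Effect measures.** Logistic regression gives an OR directly and, by standardising the fitted risks, an RR. It does not give a difference in means on the scale of the score. The MD rule in the same paragraph therefore belongs to a model that the paragraph does not name.

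**3. Covariate levels against the population.**

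| Child | Value of IBS subtype |
|---|---|
| IBS, Bristol score > 5 | IBS-D |
| IBS, Bristol score < 3 | IBS-C |
| IBS, Bristol score 3 to 5 | None given |
| FAP-NOS | None given |

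Multiple imputation, planned under Missing data, is no remedy. For a FAP-NOS child the subtype is not an unobserved value but a value that does not apply.

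**4. How many children could be affected.** The article gives no case mix, so the FAP-NOS share f is an assumption. If those children are coded as missing, the number kept is 74 × (1 - f):

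- f = 20%: 74 × 0.80 = 59.2, about 59
- f = 35%: 74 × 0.65 = 48.1, about 48
- f = 50%: 74 × 0.50 = 37

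These counts are before dropout and before any loss of IBS children scoring 3 to 5, whose number is also not stated.

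**5. Whether the loss is avoidable.** A logistic model for a simulated binary response in 74 children, with a four-level covariate (FAP-NOS, IBS-C, IBS-D, other IBS), converged and kept all 74 at each of the three assumed shares. The difficulty lies in the definition of the covariate, not in the data.

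**The case against.** The strongest reply is that this is loose wording in a secondary section. The MD rule suggests that a linear model was intended for continuous outcomes and its name left out. The article also uses IBS loosely elsewhere: attendance and absenteeism are tied to IBS symptoms although FAP-NOS children are enrolled. Subtype of IBS may therefore have been meant as subtype of FAPD. The intention-to-treat rule weighs against any reading that discards children.

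Much of this stands, and it rules out several stronger readings that a reader might infer:

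- *The adjusted analysis as a whole cannot be fitted.* Not supported. The primary outcome, stool response and compliance are binary, and logistic regression suits them.
- *Logistic regression cannot deliver the RR.* Not supported. An RR follows by standardisation, and the paragraph also allows an OR. Only the MD is out of reach.
- *The plan excludes FAP-NOS children.* Not supported. The article does not say so. Exclusion follows only if they are coded as missing, and that would conflict with the intention-to-treat rule.
- *The trial loses a quantifiable amount of power.* Not supported. The article claims no power for this additional analysis, and gives neither a control response rate nor a case mix from which to calculate a loss.

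The reply does not remove the defect. The probable intention has to be guessed, no other section supplies it, and the literal text names a wrong model for eight outcomes. This is also more than a detail left to an analysis plan, because a later plan could correct it only by departing from what is written here.

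**Conclusion.** The point holds in limited form. As written, the adjusted analysis assigns logistic regression to eight secondary outcomes that it cannot model without cut-offs the plan does not give, and it sets an MD rule that the named model cannot meet. Its third covariate has no value for FAP-NOS children or for IBS children scoring 3 to 5. Whether children are lost depends on coding. If they are coded as missing, 37 to 59 of 74 would remain for an assumed FAP-NOS share of 50% down to 20%, less any unclassified IBS children.

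This should be fixed, but it is not critical. It concerns the additional adjusted analysis. The unadjusted tests under Data analysis match their outcome types and include every child with outcomes, so the main comparison is untouched.

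**What to change.** Replace the sentence under Methods of additional analyses with two that say the following:

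1. Binary outcomes (pain response, stool response, compliance) are analysed by logistic regression, reported as an OR or as an RR by standardisation. Continuous outcomes are analysed by linear regression or ANCOVA adjusted for the baseline value where one exists, reported as an adjusted MD with 95% CI.
2. The covariates are age, sex and FAPD diagnosis, coded so that every randomised child has a value. The coding can be IBS against FAP-NOS, or four levels: FAP-NOS, IBS-C, IBS-D and other IBS.

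Either coding solves the problem. The two-level version is simpler for 74 children, and the four-level version stays closer to the covariate already named. The choice should be fixed before the allocation code is opened. The cost is two sentences of wording. No new data are needed, because diagnosis and stool consistency are already recorded at baseline.

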#### Missing data

Every effort will be made to minimize missing baseline and outcome data. However, the amount of missing data will be reported for each study arm. The reasons for withdrawals, if feasible, will be compared qualitatively between groups. Multiple imputation methods for missing data will be included to address any missing data, as recommended [13, 30, 31].

### Monitoring

#### Data and participant monitoring

The study will be performed following the protocol registered before the commencement of screening. However, in case of unexpected and valid circumstances, the protocol registry will be immediately updated and, if required, the bioethical committee will be informed.

The independent DSMB will review data after recruitment of 25, 50, and 75% of participants to review the study progress (including rate of recruitment and completeness of data) and all reported adverse events. The number of recruited children will be monitored and kept up to date. In case of an insufficient recruitment rate, defined as associated with the risk of not finishing the study within the established time (which is 2 years), we will advertise our trial among other pediatric wards and primary care physicians, however, only if adequately trained personnel is present.

#### Harms

Although the intervention is expected to be safe, all adverse events will be reported in the CRF, classified (following the International Conference on Harmonisation *Good Clinical Practice* guidelines), and evaluated for duration, intensity, and causal relationship with the intervention. Each serious adverse events will be reported to the project leader within 24 h of the notification. The project leader will notify, within 7 days, the bioethical committee, all investigators involved in the study, and the catering company responsible for the diet provision. Due to the risk of potential nutritional imbalance and growth impairment, the intervention will be guided by professionals with expertise in dietary management.

Due to the study design, involving the delivery of study diets by an outside company to each participant’s residence, the appropriate written permission of each caregiver will be obtained. Each caregiver will receive oral and written information with regard the collection and processing of personal data during and after their child’s participation in this trial.

### Ethics and dissemination

#### Research ethics approval

This protocol and the informed consent form was approved by the Ethics Committee of the Medical University of Warsaw.

#### Protocol amendments

Any modification to this version of protocol which may affect study design, sample size, study procedures, as well as benefits and harms for the participant will require a formal amendment to the protocol. Each amendment must be approved by the Ethics Committee of the Medical University of Warsaw prior to implementation.

#### Consent or assent

Written informed consent will be obtained from all participants before enrollment. The research dietitian will have a discussion with child and the child’s caregiver and answer any questions regarding the study. For children ≥13 years of age, the participants themselves can sign the informed consent; for younger children, two copies of the written informed consent will be obtained from the child’s caregiver.

#### Confidentiality

Each participant will have a participant’s identification number to maintain confidentiality. The electronic database and any electronic records will be password-protected and/or kept in password-protected folders (see Data collection and management section).

#### Access to data

Access to paper and electronic study records will be limited only to the researchers involved in this trial (AS, AH). An external independent statistician will receive an access to de-identified electronic dataset.

#### Ancillary and post-trial care

The compensation of harms will be covered by study insurance policies. For post-trial care, see Follow-up section and Fig. 1.

#### Dissemination policy – trial results

The findings of this RCT will be submitted to a peer-reviewed journal, no later than a year after the post-intervention data collection. The abstract will be submitted to relevant national and international conferences. No later than 3 years after data analysis, a full, anonymized, participant-level data set will be archived for sharing purposes. Data analysis will be completed over 3 months after RCT completion.

## Discussion

Currently, there are no evidence-based guidelines on the diagnosis and management of FAPDs in children. According to evidence in adults, use of a low-FODMAP diet is promising, however, in children the evidence is scarce [3]. RCTs involving a low-FODMAP diet are also affected by several methodological limitations (e.g., choice of control group) [11].

This study will assess the effects of a low-FODMAP diet compared with a regular diet for the management of children with FAPDs (IBS, FAP-NOS). Although high-quality evidence is needed, no study is perfect, as every RCT investigating dietary modifications of FODMAPs has had some limitations. The risk of bias associated with the possibility of the participant or caregiver guessing the nature of the provided diet using other sources cannot be excluded. To minimize this bias, a post-intervention assessment of blinding success, of both participants and researchers, has been planned (see Blinding section). A second limitation is this study involves evaluation of the first phase of a low-FODMAP diet only, without long-term follow-up. Thus far, no study conducted in children has assessed all three phases of administering a low-FODMAP diet in children with FAPDs. However, based on the clinical and research experience of this research center, such a long-term study is judged to be difficult to conduct in the pediatric population. Therefore, we decided to investigate the effectiveness and safety of only the first phase of use of a low-FODMAP diet in this RCT; however, all participants will be encouraged to continue the management of their FAPDs under the care of our research team (see Follow-up section). If feasible, clinical data from participants who choose to continue the low-FODMAP diet at our center will be collected prospectively as an independent study.

This RCT of rigorous methodological design will help to establish the effectiveness, if any exists, of the use of a low-FODMAP diet in the management of FAPDs in the pediatric population. This study will be conducted by a research center with experience in conducting both independent RCTs and trials in children with FAPDs, and in cooperation with a person who is experienced in research involving FODMAPs. The findings of this RCT will fill a gap in current evidence and inform guideline development groups about the actual efficacy of a low-FODMAP diet in the management of FAPDs in children. This RCT may also guide the direction of further research in this area.

## Data Availability

The datasets used and/or generated during this study will be made available from a given author upon reasonable request, after the publication of results, no later than 3 years from the completion of data analysis.

## Abbreviations

BMI: Body Mass Index
BW: Body weight
CI: Confidence interval
CONSORT: Consolidated Standards of Reporting Trials
CRF: Case report form
DSMB: Data and Safety Monitoring Board
FAPDs: Functional abdominal pain disorders
FAP-NOS: Functional abdominal pain – not otherwise specified
FODMAPs: Fermentable oligosaccharides, disaccharides, monosaccharides, and polyols
GSRS: Gastrointestinal Symptom Rating Scale
IBS: Irritable bowel syndrome
IBS-C: IBS with predominant constipation
IBS-D: IBS with predominant diarrhea
MD: Mean difference
MVPA: Moderate-to-Vigorous Physical Activity
OR: Odds ratio
RCI: Reliable Change Index
RCT: Randomized controlled trial
RR: Relative risk
SD: Standard deviation
SPIRIT: Standard Protocol Items: Recommendations for Interventional Trials
VAS: Visual Analogue Scale
WHO: World Health Organization
WHO-5: World Health Organization Five Well-Being Index
